## Abstract

**Background:**

People in transitional life stages, such as occupational retirement, are likely to gain weight and accumulate abdominal fat mass caused by changes in physical activity and diet. Hence, retirees are an important target group for weight gain prevention programmes, as described in the present paper.

**Methods/Design:**

A systematic and stepwise approach (Intervention Mapping) is used to develop a low-intensity energy balance intervention programme for recent retirees. This one-year, low-intensity multifaceted programme aims to prevent accumulation of abdominal fat mass and general weight gain by increasing awareness of energy balance and influencing related behaviours of participants' preference. These behaviours are physical activity, fibre intake, portion size and fat consumption. The effectiveness of the intervention programme is tested in a cluster randomised controlled trial. Measurements of anthropometry, physical activity, energy intake, and related psychosocial determinants are performed at baseline and repeated at 6 months for intermediate effect, at 12 months to evaluate short-term intervention effects and at 24 months to test the sustainability of the effects.

**Discussion:**

This intervention programme is unique in its focus on retirees and energy balance. It aims at increasing awareness and takes into account personal preferences of the users by offering several options for behaviour change. Moreover, the intervention programme is evaluated at short-term and long-term and includes consecutive outcome measures (determinants, behaviour and body composition).

## Background

This study is performed as part of the Netherlands Heart Foundation 'Netherlands Research programme for weight Gain prevention' (NHF-NRG). This multidisciplinary programme aims to gain insight into behavioural determinants of weight gain and to identify potentially effective methods and strategies for the prevention of weight gain in distinct target groups: adolescents, young adults and recent retirees [1].

Overweight and obesity are associated with chronic conditions such as diabetes, hypertension, cardiovascular diseases and certain types of cancer, and thus considered a major public health concern [2]. Many attempts have been made to treat overweight and obesity and although these attempts show short term weight loss in most subjects, weight is often regained after cessation of the intervention [3,4]. Therefore, it has been suggested that prevention of weight gain in the general population may be a more effective strategy for addressing the overweight and obesity epidemic [5-11]. However, studies testing weight gain prevention programmes among adults are limited and often not successful. A review by Hardeman *et al *[12] regarding interventions to prevent weight gain shows that the interventions exhibited various degrees of effectiveness. Furthermore, it is not clear what elements of the interventions are associated with increased effect size, since only one of the five studies that involved an RCT design reports a significant effect on weight. The authors plead for more objective measures of physical activity and diet in future studies and for longer periods of follow-up [12].

Programmes to prevent weight gain should focus on the balance between physical activity and energy intake from foods, also referred to as energy balance [13]. Target groups are segments of the population at elevated risk of weight gain. These are often populations going through transitional life stages [1,10,14], leading to changes in daily routine. Occupational retirement is such a transitional life stage. Retirees lack work-related physical activity, which may not be compensated after retirement. Moreover, they have increased access to food and more opportunity for eating. Since, apart from retirement, ageing itself can also lead to increased fat mass and to decreased skeletal muscle mass [15,16], retirees are an important group for weight gain prevention.

This paper presents the development of the intervention programme and the study design of the cluster randomised controlled trial, called the Wageningen Approach against fat Accumulation and weight Gain (WAAG-Study). The main aim of the programme is to prevent weight gain, in particular accumulation of abdominal fat mass in recent retirees by increasing awareness of energy balance and subsequently adapting energy balance-related behaviours according to participants' preferences.

## Methods/Design

### Participants and recruitment

Participants for this study are recruited from pre-retirement workshops offered by employers to approximately 10% of Dutch retirees. During such a five-day workshop several topics are discussed in order to prepare retirees for the new phase in life, e.g. changes in the household after retirement, health and vitality, and their new role in society. Inclusion criteria for the present study are: age between 55–65 years, recently retired, defined as maximal six months before or after date of retirement at inclusion, apparently healthy and not undergoing any medical treatment that might affect the outcome measures. Written informed consent from participants is obtained upon enrolment. The study protocol is approved by the Medical Ethics Committee of Wageningen University.

### Study design

We randomise all participants from one workshop together rather than individually because we fear adoption of the intervention programme by individuals in the control group. Thus, clusters of workshop participants are allocated to either the intervention or control group. Allocation is performed the week following baseline examination by an independent person and taking into account the number participants per workshop and the number of included clusters per week.

We hypothesise that waist circumference in the control group will increase with 0.5 cm per year (standard deviation = 1.3 cm) while it will remain stable among subjects in the intervention group. This is based on data obtained from a middle-aged (56–65 years) Dutch population from the 'Doetinchem Cohort' (National Institute for Public Health and the Environment, Bilthoven, the Netherlands). Calculations reveal a sample size of a total of 400 individuals, taking into account 80% power, cluster randomisation [17] with an estimated design effect of 20% [18] and assuming a drop out of 25%.

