### Statistical analysis

Analyses will be based on the intention-to-treat principle. Because of the cluster randomisation, we will use multilevel analyses (SAS PROC MIXED), with cluster as the random intercept. Baseline values of the dependent variable will be included as covariates. Furthermore, we plan to perform secondary analyses to explore intervention effects in subgroups of gender, education, body fatness and activity at latest job [60-62]. Finally, adherence to the intervention, defined as the self-reported use of the intervention materials (range 0–5), may be related to the outcome measures.

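### The allocation uses workshop size and clusters per week but the stated model names neither, so its interval is somewhat too wide if either predicts waist change

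*Protocol article*

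**What the plan says.** Under Study design, the protocol article randomises whole workshops: "clusters of workshop participants are allocated to either the intervention or control group". An independent person does this in the week after the baseline examination, "taking into account the number participants per workshop and the number of included clusters per week". The article does not say how the two counts are used; it names no strata, blocks or minimisation rule.

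Under Statistical analysis, the article says "we will use multilevel analyses (SAS PROC MIXED), with cluster as the random intercept". The one adjustment named is the baseline measurement: "Baseline values of the dependent variable will be included as covariates". Workshop size and inclusion week are not mentioned there, and the article does not say that its list of covariates is complete.

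**The concern.** When the allocation evens out a factor between the arms, that factor adds little or nothing to the chance variation of the arm difference. A model without the factor still counts its effect as between-cluster error, so the reported standard error exceeds the true one whenever the factor predicts the outcome. In this trial the comparison is between workshops, and unexplained between-cluster variance feeds directly into the interval. Inclusion period could plausibly matter through season or measuring round, and workshop size through the type of employer or group. What is at stake is precision that the design has earned and the analysis does not credit. The validity of the result is not in question.

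**Working it through.** **Inputs from the article (Study design).** Difference 0.5 cm at one year; standard deviation 1.3 cm; power 80%; design effect 20%, read as 1.2; dropout 25%; total 400.

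**Assumptions.** Two-sided alpha 0.05; equal arms; 32 or 48 equal clusters; four recruitment blocks balanced between arms; a share *s* of the between-cluster variance explained by the allocation factors. The article gives none of these.

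**The plan's own figure.** Per arm: 2 × (1.96 + 0.84)² × 1.3² / 0.5² ≈ 106, or 107 with rounding up, so 214 in total. Then 214 × 1.2 = 256.8, and 256.8 / 0.75 ≈ 343. The stated 400 is not reproduced; it is larger than these inputs require. This does not affect the present point, for which only the completers matter: 400 × 0.75 = 300.

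**Reported standard error without the factors.** 2 × 1.3 × √(1.2 / 300) = 0.164 cm.

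**True standard deviation of the arm difference when the factors are balanced.** With *m* completers per cluster, a design effect of 1.2 implies an intracluster correlation of 0.2/(m − 1). Balancing a share *s* removes s × m × 0.2/(m − 1) from the 1.2. Thus V = 1.2 − s × 0.2m/(m − 1), and the true SD is 2.6 × √(V/300). For 48 clusters m = 300/48 = 6.25 and V = 1.2 − 0.238s. For 32 clusters m = 300/32 = 9.375 and V = 1.2 − 0.224s.

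**Power.** Without the factors: Φ((0.5 − t × 0.1644)/SD), with t on K − 2 degrees of freedom for K clusters. With the factors: Φ(0.5/SD − t), with t on K − 6. The 4 degrees of freedom are three for the four blocks and one for workshop size. Type I error without the factors: 2 × (1 − Φ(1.96 × 0.1644/SD)).

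| Clusters | Share s | V | True SD | Reported / true | Type I error, unadjusted | Power unadjusted | Power adjusted |
|---|---|---|---|---|---|---|---|
| 48 | 0 | 1.200 | 0.164 | 1.00 | 0.050 | 0.848 | 0.847 |
| 48 | 25% | 1.140 | 0.160 | 1.03 | 0.044 | 0.854 | 0.865 |
| 48 | 50% | 1.081 | 0.156 | 1.05 | 0.039 | 0.861 | 0.882 |
| 48 | 100% | 0.962 | 0.147 | 1.12 | 0.029 | 0.875 | 0.916 |
| 32 | 0 | 1.200 | 0.164 | 1.00 | 0.050 | 0.841 | 0.838 |
| 32 | 25% | 1.144 | 0.161 | 1.02 | 0.045 | 0.847 | 0.855 |
| 32 | 50% | 1.088 | 0.157 | 1.05 | 0.040 | 0.853 | 0.872 |
| 32 | 100% | 0.976 | 0.148 | 1.11 | 0.030 | 0.866 | 0.906 |

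These approximations agree with cluster-level simulations at a design effect of 1.2. With clusters paired by week (30 or 50 clusters, 40,000 runs per setting), the unadjusted type I error was 0.044 to 0.046 at a 25% share, 0.040 to 0.041 at 50% and 0.029 to 0.030 at 100%. With four coarse blocks, the gain from adjustment at a 50% share was about 1 to 2 points of power. The table assumes that the blocks capture the whole share; if they capture less, the gain is smaller, hence a lower end of about 0.5 points.

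**How fine the period should be.** Adjusting for every week-pair halves the cluster-level degrees of freedom: from 48 to 24 with 50 clusters, from 28 to 14 with 30. In the paired simulation this cost about 2 to 3 points when the factor explained nothing (0.845 to 0.829 and 0.834 to 0.806). At a 50% share it gained one point or nothing (0.858 to 0.868 and 0.842 to 0.841). Coarse blocks avoid most of that cost.

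**The case against.** **This is a condensed article.** A full covariate list may sit in an analysis plan that is not shown, so silence is not proof of exclusion. That stands as a caution. The point survives as a modest one because the article does state a model, with its procedure, random effect and covariate, and separately states what the allocation uses; the first does not follow the second.

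**Blocking by week is an inference.** The text names two counts and no method. Keeping the arms even in size is also a natural reading, and on that reading there may be no week stratum to carry into the model. This stands, and is why the conclusion is conditional.

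**Season is not the allocation factor.** A coarse period only approximates the week and recovers only the variance between blocks. That is true, but single weeks cost too many degrees of freedom, and a week holding one cluster would absorb that cluster entirely. Season should also largely cancel in 12- and 24-month changes, though not necessarily at 6 months.

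**Stronger readings that a reader might infer, and that the article does not support:**

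- *The error structure does not match the randomisation.* It does: workshops are allocated, and the workshop is the random intercept. Any discrepancy needs size or period to predict the outcome, which the article does not show.
- *The balancing effort is wasted.* The true SD falls from 0.164 to about 0.147 as the balanced share rises, whether or not the model adjusts. Only the reported standard error fails to show it.
- *Adjustment is worth 17 to 50 of the 400 participants.* That comes from lowering the design effect to 1.15, 1.10 or 1.05 and multiplying the relative saving by 400. It treats a fall in reported variance as a fall in true variance, which the balanced allocation has already delivered.

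**Conclusion.** The point holds as a minor one. As written, the model does not carry the two quantities used in the allocation. If either predicts waist change, the standard error is conservative: about 2% to 12% too wide for shares of 25% to 100% at the planned design effect, with type I error of about 0.03 to 0.046 and about 0.5 to 4 points of power forgone. There is no bias and no inflated type I error. If neither predicts the outcome, nothing is lost by leaving them out.

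The size rests on assumed shares, an assumed number of clusters and the reading that the allocation balances the arms on these factors. Shares near 100% are an upper limit, not an expectation. Larger losses (9 to 25 points, with week-pair adjustment) appear in the simulations only at a design effect of 2.0 with half or all of the clustering due to the factor, well beyond what the article plans for.

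**What to change.** In Statistical analysis, add workshop size and a coarse inclusion period (for example season or recruitment block, not single weeks or pairs) as fixed effects in the primary PROC MIXED model, and fix this before outcome data are seen. In Study design, add a sentence on how the two counts enter the allocation. If they serve only to keep arm sizes even and the factors are left out of the model, say so and give the reason.

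The data are already held, and the text is about a sentence in each section. The statistical cost is about 4 cluster-level degrees of freedom: roughly 0.2 points of power if the factors explain nothing (0.1 with 48 clusters and 0.3 with 32 in the table above).

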### Theoretical basis of the intervention programme

The intervention programme is developed according to the Intervention Mapping protocol that facilitates a systematic, stepwise process of designing health behaviour interventions [19]. Basically, it comprises of a needs assessment of the study population, an inventory of factors that influence health behaviour, a definition of the main aim, a subdivision into practicable behaviours, a linkage to determinants of behaviour, a translation into methods and practical strategies and the development of a detailed program plan.

The main aim of the intervention programme is to prevent weight gain and in particular accumulation of abdominal fat mass. Practicable intermediate steps to reach this aim are increased awareness of energy balance and related behaviours and subsequently prevention of unfavourable change in diet and/or physical activity. For the purpose of intelligibility, energy balance is defined as the equilibrium between energy intake from the diet and energy expenditure from physical activity. Specific energy balance-related behaviours that are identified for the present study are depicted in figure 1 and elucidated below.

The intervention programme focuses on two domains of physical activity: daily routine physical activity and recreational/sport activities. Daily routine physical activity is of importance, since retirees lack work-related physical activity that may not be compensated after retirement. Therefore, retirees need to be aware of opportunities for daily physical activity, such as household activities and active transportation [20,21]. Furthermore, retirees have more time available and thus recreational and sport activities, e.g. bicycling and walking, are also incorporated in the programme.

Two strategies related to energy-density are included in the programme: replacement of high-fat foods with low-fat foods [22-27] and replacement of low-fibre foods with high-fibre foods [26,28-31]. The intervention programme also focuses on the reduction of portion sizes of energy dense foods during the main meals of the day and during snacking [32,33].

The behaviours mentioned above are further linked to their matching psychosocial determinant: knowledge, awareness, attitude, perceived self-efficacy, and habit. In our study, knowledge is further subdivided in nutritional knowledge [34], knowledge of fibre-rich products [35] and knowing health benefits of a healthy diet and physical activity. Previous studies have shown that increasing awareness of personal physical activity and dietary behaviours is important [36,37] as well as attitude [38-41]. Furthermore, perceived self-efficacy has been shown to be a predictor for the consumption of fruits, vegetables and low fat diets [42] and may affect the consumption of large portion sizes [43]. Finally, habit is a factor that needs to be taken into account, since dietary behaviour has often become a habit since childhood [38,44,45] and it may also influence behavioural choices regarding physical activity [46,47].

### Intervention materials

Based on the linkage of determinants of energy balance-related behaviour to methods and strategies, existing materials are identified and new materials are developed. This resulted in our energy balance programme, that has a low-intensity, multifaceted character and is disseminated to the intervention group over a period of one-year (see table 1 for a detailed description of the programme). Figure 2 shows the moments of distribution of the materials. The first element in the programme is a toolbox that contains an instruction leaflet and several instruments to increase awareness and knowledge of personal status of physical activity, dietary intake and weight. The second element is a CD-ROM that contains stage-matched computer tailored feedback on current energy balance status. This feedback also incorporates attitude and self-efficacy [48,49]. The outcome of the test and/or personal preference can be employed in the subsequent element, a second CD-ROM. This also contains a computer tailored programme and offers four different options for feedback on personal behaviour:

1. Feedback on total physical activity, including daily routine and sport activities;

2. Feedback on fibre intake;

3. Feedback on portion sizes of energy dense foods (hot or cold meals, snacks or beverages);

4. Feedback on fat intake (hot or cold meals, snacks).

Thus, participants can choose to receive individual feedback on one or more options. The feedback consists in all cases of a letter that states the current status compared to the norm (e.g. the norm for fat intake in the Netherlands, or minutes of physical activity per day). Participants can print this letter and can also choose to formulate an action plan for physical activity and can use the low-fat recipes that are available on the second CD-ROM.

Apart from the tool box and CD-ROMs, participants of the intervention group receive printed newsletters with information on the study and encouragements and prompts to use the materials and choose another option from the second CD-ROM. They also have access to the study's website, with login facilities for additional information and the Weight Co@ch, an interactive programme developed by TNO Quality of Life [50].

Subjects of the control group receive newsletters with general information only, e.g. announcements for art exhibitions and have limited access to the website.

### Outcome measurements

The effectiveness of the intervention programme is evaluated as shown in figure 2 using various consecutive outcomes as depicted in figure 3. In brief, data on body composition, blood pressure, diet and physical activity are collected at all four periods, whereas data on psychosocial determinants are gathered at baseline and after 6 and 12 months only. More details about the measurements are provided below.

#### Questionnaires

At baseline, data on demographical factors, such as education, date of retirement, and marital status are collected, as well as information on perceived health, smoking habits, use of hormone replacement therapy for women and drug use for high cholesterol levels, high blood pressure and diabetes mellitus.

Psychosocial determinants are assessed for all five identified behaviours (see figure 1) separately. Attitude, social support, norms and pressure, and self-efficacy expectations are determined based on commonly used constructs of the cognitive factors from the Theory of Planned Behaviour [51]. Intention to change and the stage of change for the five behaviours are also assessed; the assignment to stage of change being based on a combination of the Precaution Adoption Process Model [52,53] and the TransTheoretical Model [54]. Habit strength is assessed based on the Self-Report Habit Index [55] using three indicators of habit.

Data on dietary intake are collected using a self-administered semi-quantitative Food Frequency Questionnaire [56]. From these data total energy intake, total fat intake, saturated, mono- and poly-unsaturated fatty acids, cholesterol, total protein, total carbohydrate and alcohol consumption are derived. Fruit and vegetable intake (gram/day) is used to approximate fibre consumption. Portion size for energy dense foods is calculated as number of servings divided by the frequency of consumption.

Physical activity is assessed using the self-administered Dutch version of the Physical Activity Scale for the Elderly (PASE) [57]. The PASE assesses physical activity in the previous week in older people (aged 65–100 years) and specifically includes activities of the daily living, such as household activities [57,58]. The questionnaire assesses frequency and duration of activities at several intensities resulting in the PASE score that ranges from 0–400 with higher scores indicating greater activity levels [58].

The process evaluation is based on Rogers' diffusion of innovations-model [59] and data are collected at all follow-up measurements by using questionnaires monitoring the intervention delivery, participation, comprehension, satisfaction, level of use, and fidelity.

#### Anthropometry

Baseline physical examinations are conducted at the location of the pre-retirement workshops. Immediately after the one-year intervention participants are re-examined. To test the sustainability of the effects participants are measured again one year after the cessation of the intervention programme (see top part figure 2). Follow-up examinations are mostly performed at community health centres throughout the Netherlands, at the same time of day and by the same researcher compared to baseline.

Physical examinations are conducted between 11.00 am and 2.00 pm with participants wearing underwear only. Body weight is measured to the nearest 0.2 kg with an electric weigh-beam (SECA 840 scale & SECA 888; Vogel & Halke GmbH & Co KG, Hamburg, Germany) and body height to the nearest 0.1 cm with a mobile stadiometer (SECA 225; Vogel & Halke GmbH & Co KG, Hamburg, Germany). Waist circumference is measured at the midpoint between the lower rib and the iliac crest, hip circumference at the trochanter level, and thigh circumference immediately below the gluteal fold, upper arm circumference at the midst between the acromion and olecranon and calf circumference between the knee and ankle malleoli, with the leg at a 90° angle. Circumferences are measured twice to the nearest 0.1 cm with a plastic measuring tape. These anthropometric measurements are taken with participants in an upright position. Abdominal sagittal diameter is measured twice at the midst between the lower rib and iliac crest with participants in a supine position.

